### Randomization and blinding

Randomization is carried out in concealed envelopes by a computer-generated randomization list generated by a research assistant who is not involved in the participant’s clinical management. Randomization will be done in a 1:1 ratio in blocks, stratified according to D3 or D5 embryo transfer. On the D3 of the HRT-FET cycle, the investigators get a concealed envelop by different blocks in sequence to obtain the randomization numbers and allocate groups for the eligible patients. Participants will be randomized into one of the two groups on the D3 when serum progesterone is less than 7.24μg/L, if the intervention group has intramuscular progesterone 40 mg per day from D3 to weeks 8 if clinical pregnancy, and if the control group has no extra intervention. The clinicians, nurses, and the participants all will not be blinded to the treatment allocation. The statistician is blinded to the group allocation.

### Procedures

#### Study protocol (endometrial preparation)

All the included patients receive HRT for endometrial preparation. Treatment starts on day 2 or day 3 of menstruation with oral estradiol valerate administration (Progynova®, Bayer Guangzhou, China)—constant dose 4–8 mg/d or step-up increasing dose protocols, and the endometrium thickness will either be checked once during the first 5–7 days. The estradiol dose will be adjusted accordingly. After about 10–14 days of estrogens, a transvaginal ultrasound will be performed to measure the endometrial thickness and to confirm a triple layer pattern. Patients are considered ready for ET once endometrial thickness reaches 8 mm, and quiescent ovaries are detected by ultrasound, serum E2 > 150 pg/mL, and the serum P level < 2 ng/mL. Transvaginal P (Utrogestan® Besins, France) will be administered 3 or 5 days before embryo transfer at a dose of 200 mg tid or 400 mg bid Utrogestan vaginally. Transvaginal progesterone will be started 3 days before embryo transfer for patients who will have day 3 embryo transferred or 5 days before embryo transfer for those who will have day 5 embryo transferred. Serum progesterone will be tested on the morning of D3 (after 3 days of progesterone addition) after the first dose of progesterone, approximately 2 h beforehand. In case of pregnancy, HRT was maintained until gestational weeks 10. The estrogen would be gradually decreased with dosage after gestation at 8 weeks. The progesterone dosage would be not changed.

#### Selecting patients

On the first day of progesterone supplementation (day 0), eligible patients are selected for this study. After checking all the inclusion and exclusion criteria, patients will be informed about the nature of the study, read the informed consent (IC) form, and decide if they wish to participate. After signing the IC form, a blood test of progesterone is performed on day 3. According to the serum progesterone level on day 3, if P is ≥ 7.24 ng/mL, continue with the transvaginal progesterone until the pregnancy test on days 14–16. If P < 7.24 ng/mL, according to the randomization numbers, the patient is randomized to either non-intervention control group or intervention group with intramuscular progesterone 40 mg until the pregnancy test on days 16–17. This protocol will continue until gestation week 8 and withdraw the intramuscular progesterone.

The included patient should test the serum progesterone level on D3 no matter which day the embryo transfer will be performed. According to the progesterone level, there are two groups:
Group A: serum progesterone < 7.24μg/L, followed by randomized:
A1: plus additional treatment (intramuscular progesterone 40 mg per day from D3)A2: without additional treatmentGroup B: serum progesterone ≥ 7.24μg/L, without additional treatment

Samples will be tested by the Beckman chemiluminescence method (Beckman DXI800, Roche, USA). The intra- and inter-assay variation coefficients for the P determinations were 6.11–11.19% and 7.51–9.57%, respectively, for *P* values between 1.26 and 22.61 ng/mL. The intra- and inter-assay variation coefficients for the E2 determinations were 2.4–10.5% and 2.4–9%, respectively, with a measurement range of 50–120 pg/mL.

#### Endpoints

All the parameters were defined according to the ICMART and WHO Revised Glossary on ART [9].

The primary endpoint was OPR beyond gestational weeks 12 in HRT-FET cycles.

The secondary endpoints were serum P (ng/mL) and estradiol (E2, pg/mL) on D0, endometrial thickness (mm), implantation rate (number of gestational sacs seen in a transvaginal ultrasound/number of embryos transferred per patient), clinical pregnancy (presence of at least one gestational sac intrauterine in ultrasound), and miscarriage rate (any clinical pregnancy lost before gestation weeks 12).

- Pregnancy: positive pregnancy test, HCG level beyond 20 U/L after 14 days of ET

- Clinical pregnancy: the presence of intrauterine gestational sac on pelvic ultrasound at 6 weeks of gestation

- Biochemical pregnancy: a pregnancy diagnosed only by the detection of HCG in serum or urine and that does not develop into a clinical pregnancy

- Implantation rate: number of intrauterine gestational sacs per embryo transferred

- Ongoing pregnancy: viable pregnancy beyond gestation 12 weeks

- Multiple pregnancy, ectopic pregnancy, miscarriage, pelvic infection, fetal or congenital defects, obstetric complications, and birth weight of babies

#### Data collection and follow-up protocol

All data will be recorded in CRF and will be collected at four specific moments: upon recruitment (V0), on the D3 randomization (V1), after the ultrasound at 6–7 weeks’ gestation to confirm the clinical pregnancy (V2), and after a telephone call beyond 12 weeks of gestation and until delivery for follow-up of women who have a clinical pregnancy confirmed at 6–7 weeks (V3).

#### Assessment of safety

We do not expect to have undesirable or serious undesirable events related to the study and its proceedings. Indeed, all procedures included in this study are standard procedures and will be performed in accordance with the national guidelines and recommendations. HRT-FET cycle is common in clinical practice. Adverse effects such as local tenderness, swelling, nodular formation, and even local tissue necrosis are few with the intervention group after intramuscular progesterone injection. These adverse effects will be recorded.

### Statistical analysis

Statistical analysis will be performed by using the Statistical Package for the Social Sciences version 22.0 (SPSS Inc., Chicago, IL, USA). A descriptive analysis of the population’s characteristics will be performed. Demographic features of the two study groups will be compared. The chi-square test and Fisher’s exact test will be used for categorical variables. ANOVA test or the Kruskal-Wallis *H* test will be used to compare the continuous variables between the two groups. Comparison of categorical variables will be expressed as numbers with percentages. The results of continuous variables will be reported as mean values and standard deviations, or medians with 25th and 75th percentile. All statistical tests will be bilateral, and a *P* value < 0.05 will be considered statistically significant.

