### Patient population

This study will recruit infertile patients undergoing HRT-FET cycle. All the patients will be performed a single or double embryos transfer in the cleavage or blastocyst stage. The eligibility criteria are as follows.

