### Sample size calculation

A power analysis was performed according to the results from our own retrospective analysis, concluding a significant decrease in clinical pregnancy rate (CPR) when progesterone was < 7.24 μg/L (the first quartile) of 34.67% compared with ≥ 7.24 μg/L of 51.55% (*P* = 0.029).

The sample size was calculated in a two-sided test (80% statistical power, 95% confidence interval).

Low serum progesterone group: 1:1 intervention (A1) and control group (A2); high serum progesterone group: 1:1 to control group (B)

Group sample sizes are separated: 134 in group A1 and 134 in group A2 and 134 in group B. The test statistic used was the two-sided Fisher’s exact test. The significance level of the test was targeted at 0.05.

The formula is as follows:
$$ n=\frac{{\left({Z}_{1-\alpha }+{Z}_{1-\beta}\right)}^2\times \left({p}_1\left(1-{p}_1\right)+{p}_2\left(1-{p}_2\right)\right)}{{\left(\varepsilon -\delta \right)}^2} $$

After considering 5% of dropouts, 432 patients were recruited in total.

Age, BMI, endometrial thickness, serum E2, and number of transferred embryos were included in the analysis, regardless of their *P* values. Biochemical pregnancy is defined as serum HCG level ≥ 20 U/L. Clinical pregnancy is defined as observable gestation sac by transvaginal ultrasound. Ongoing pregnancy is defined as clinical pregnancy beyond gestational week 12.

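### Randomisation is stratified by D3/D5 transfer, but the only tests stated for a binary outcome ignore that stratum and cannot carry the covariates named in the sample size section

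*Protocol article*

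**What the plan says.** All of this is in the protocol article.

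- **Randomization and blinding:** "Randomization will be done in a 1:1 ratio in blocks, stratified according to D3 or D5 embryo transfer". Allocation takes place on D3 of progesterone. It is open: "The clinicians, nurses, and the participants all will not be blinded to the treatment allocation".
- **Selecting patients:** "The included patient should test the serum progesterone level on D3 no matter which day the embryo transfer will be performed". A patient in the D5 stratum is therefore tested and allocated about two days before transfer; a patient in the D3 stratum is allocated on the day of transfer.
- **Patient population:** "All the patients will be performed a single or double embryos transfer in the cleavage or blastocyst stage".
- **Endpoints:** the primary endpoint is the ongoing pregnancy rate (OPR) beyond week 12, a binary outcome.
- **Statistical analysis:** chi-square is named, and Fisher's "exact test will be used for categorical variables". No stratified test and no regression model is mentioned.
- **Sample size calculation:** the two-sided Fisher's exact test is the test statistic. The section also says "Age, BMI, endometrial thickness, serum E2, and number of transferred embryos were included in the analysis, regardless of their" P values. D3/D5 transfer is not among these five variables.

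**The concern.** Two things do not fit together.

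First, the design balances the arms within D3 and D5 transfers, but the stated analysis discards that information. When the stratum predicts outcome, balancing on it reduces the true variability of the difference between arms. An unstratified test still uses the larger variance, so it rejects too rarely under the null hypothesis and gives up some power.

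Second, neither a chi-square nor a Fisher test can adjust for anything. If the covariate sentence describes the trial, the article implies two different analyses of the same endpoint: one unadjusted, the other adjusted for five variables by a model that is not described. Unless one is declared primary in advance, the choice is open once data are seen. The blinded statistician does not settle which analysis is primary.

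One of the five variables also needs care. The number of embryos transferred is observed at transfer, which in the D5 stratum comes after an open allocation. If knowledge of the arm affected it, adjusting for it would condition on a consequence of allocation.

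**Working it through.** **1. The plan's own figure.** Inputs from Sample size calculation: p1 = 0.3467 and p2 = 0.5155 (clinical pregnancy rates), two-sided alpha 0.05, power 80%. The usual unstratified pooled formula is

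n = [z(0.975) × √(2p̄(1−p̄)) + z(0.80) × √(p1(1−p1) + p2(1−p2))]² / (p2−p1)²

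With p̄ = (0.3467 + 0.5155)/2 = 0.4311, the two terms are 1.3727 and 0.5808, and (1.3727 + 0.5808)² / 0.1688² = 133.9, so **134 per group**. The stated figure is reproduced, and by a calculation that also ignores the strata. Exact power at 134 per group is 81.0% for the Pearson chi-square and 77.5% for the Fisher test that the section names.

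**2. Cost of ignoring the stratum.** The article gives neither OPR by transfer day nor the stratum shares. Assumptions: two equal strata; exact balance within strata; mean control rate 34.67%; a common within-stratum odds ratio of (0.5155/0.4845)/(0.3467/0.6533) = 2.00; and a D5−D3 gap in control rate of 0 to 40 points. For each scenario, 200,000 trials of 134 per arm were simulated and analysed by the unstratified Pearson chi-square and by the Cochran-Mantel-Haenszel (CMH) test.

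| D5−D3 gap | Type I error: Pearson | Type I error: CMH | Power: Pearson | Power: CMH | Power lost |
|---|---|---|---|---|---|
| 0 | 4.9% | 5.0% | 81.1% | 80.7% | none |
| 10 points | 4.7% | 4.9% | 80.1% | 80.2% | under 0.1 |
| 20 points | 4.4% | 5.0% | 77.7% | 78.2% | 0.5 |
| 30 points | 3.8% | 5.0% | 72.9% | 75.3% | 2.4 |
| 40 points | 3.0% | 5.1% | 64.1% | 70.7% | 6.6 |

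Read the power columns across each row. Both fall down the table because a fixed odds ratio gives a smaller difference in rates as the strata move apart; that fall is not the cost of the test. With the Yates correction, which behaves much like Fisher's test, type I error goes from 3.7% at no gap to 2.2% at 40 points, and power from 77.5% to 58.8%.

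**3. Check by hand under the null hypothesis.** With equal strata and gap d, the share of outcome variance between strata is s = (d²/4) / (0.3467 × 0.6533) = (d²/4)/0.2265. The unstratified test overstates the standard error by a factor 1/√(1−s), so its type I error is about 2[1 − Φ(1.96/√(1−s))].

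- d = 0.20: s = 0.0100/0.2265 = 4.4%; √(1−s) = 0.978; 1.96/0.978 = 2.00; type I error 4.5%.
- d = 0.40: s = 0.0400/0.2265 = 17.7%; √(1−s) = 0.907; 1.96/0.907 = 2.16; type I error 3.1%.

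Both agree with the simulation.

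**4. When each named covariate is known.** Age and BMI are baseline. Endometrial thickness has a D0 eligibility limit, and E2 is listed for D0; both come before allocation on D3. The number of embryos transferred becomes a fact at transfer: the same day as allocation for D3 transfers, about two days later for D5 transfers. The article does not say when that number is decided.

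**The case against.** The case for leaving the plan alone has several parts, and some of it stands.

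- **No test is tied to OPR by name.** The Statistical analysis section is generic, and the sample size section names Fisher only for the calculation. This is true. But OPR is binary, these are the only tests offered for such an outcome, and the two sections agree. A separate analysis plan may say more; the point rests on what the article states.
- **The covariate sentence may describe the retrospective study.** It is in the past tense, in a section that opens with that study. The same section also uses the past tense for the planned total of 432, and trial outcome definitions follow directly, so the wording does not decide the matter. If the sentence is retrospective, the mismatch with the Statistical analysis section and the concern about embryo number both fall away, and the unused stratum remains.
- **Validity is not threatened.** This stands. A reader might infer that ignoring the strata inflates false positives; the effect is the opposite.
- **The loss may be trivial.** This stands for moderate gaps. A reader might assume that cleavage or blastocyst stage is strongly prognostic here and that much power is wasted. The article gives no rates by transfer day, and up to a 20-point gap the loss is below 1 point.
- **Embryo number may be fixed before allocation.** Eligibility is checked on day 0, and nothing says when the number is settled. A reader might infer that clinicians choose it on D5 with the arm known. Only the order of allocation and transfer is documented; the timing of the decision is not.

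**Conclusion.** The point holds in a limited form. The stated tests do not use the factor on which randomisation was stratified, and they cannot accommodate the covariates that the sample size section lists. Those two sections should be reconciled.

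The statistical cost is conservatism and usually a small loss of power, of the size tabulated above. It depends on the assumed equal strata, common odds ratio and D3-D5 gap, none of which the article supplies. It is not an inflated error rate, and this point alone does not show that the trial is underpowered: on the stated rates, 134 per group is reproduced. The named Fisher test, at 77.5%, nevertheless leaves no margin to give away.

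The embryo-number concern is conditional on two things: that the covariate sentence applies to the trial, and that the number was not settled before allocation. Influence by arm is then possible in the D5 stratum; it is not established.

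**What to change.** 1. Name one primary analysis of OPR for A1 v A2, stratified by D3/D5 as recorded at randomisation. Either use a CMH test with a Mantel-Haenszel risk difference and 95% CI, or a logistic regression with the stratum plus age, BMI, D0 endometrial thickness and D0 E2.
2. Keep the unstratified chi-square or Fisher test as a sensitivity analysis.
3. State whether the covariate sentence in Sample size calculation refers to the retrospective analysis or to the trial. If it refers to the trial, move it to Statistical analysis and name the model.
4. Leave the number of embryos actually transferred out of the primary model unless records show that it was fixed before allocation.

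The cost is a few sentences in the protocol or analysis plan, settled before outcomes are examined by arm. The stratum is known from the randomisation, and the four pre-allocation covariates are already named in the article. More than 300 subjects had been enrolled when the article was prepared, so a new field for the planned number of embryos could not be filled prospectively for them. The Mantel-Haenszel option, or a model without embryo number, avoids that problem.

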### Expected repercussions

If OPRs in the intervention group with low serum progesterone are significantly higher than that in the control group, it will provide a valuable evidence for HRT-FET practice. If OPRs were to be comparable between the three groups, the serum progesterone level is not predictive of the outcome.

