There are several different kinds of exogenous progesterone such as intramuscular, orally, vaginally, and trans-rectum [5]. The vaginal progesterone has been most widely used in ART because of its convenience and uterine first-pass effect. Vaginal P rapidly reaches the systemic circulation, and the steady state in the serum is achieved around 48–50 h such as Utrogestan 600 mg in a day, so its serum measurement on the day of ET seems reliable. Besides, a previous study showed that increasing doses of vaginal P do not proportionally increase serum concentrations [6]. In fact, the uptake, absorption, and metabolism of progesterone can vary among individualized patients [3]. If there is an optimal serum progesterone level, this problem might be solved by increasing the P dose from the very beginning or other optimal times, but has not yet to be demonstrated. The latest prospective study concluded that low serum progesterone on the day of embryo transfer was associated with a diminished ongoing pregnancy rate in oocyte donation cycles after artificial endometrial preparation [7]. We raised the question that if progesterone added on the day of ET can improve the outcome. So, it is necessary to explore this issue in the prospective controlled study.

According to this background, we design a prospective study to explore if serum P levels on the day of ET are related with clinical pregnancy and ongoing pregnancy rate, and additional progesterone intervention is helpful to improve the outcome.

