## Methods/design

### Study design

The study is designed as a randomized controlled trial. Eligible patients will be recruited in this study and checked the serum progesterone on the day of embryo transfer. According to the serum progesterone, the patients with low serum progesterone will be randomly assigned to the intervention group or the control group with a 1:1 ratio (see Fig. 1).

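### Reading comparable ongoing pregnancy rates in three groups as proof that serum progesterone is not predictive would treat an inconclusive result as a negative one

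*Protocol article*

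**What the plan says.** The Background gives the study two aims. One is to "explore if serum P levels on the day of ET are related with clinical pregnancy and ongoing pregnancy rate"; the other is to see whether added progesterone helps. Under Study design, "the patients with low serum progesterone will be randomly assigned to the intervention group or the control group with a 1:1 ratio". Selecting patients defines three groups by day-3 serum progesterone. A1 (low, randomised to added progesterone) and A2 (low, randomised control) lie below 7.24 μg/L. B lies at or above it and, like A2, is followed "without additional treatment".

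Expected repercussions then fixes two readings of the result. The first compares intervention with control among low-progesterone patients. The second is "If OPRs were to be comparable between the three groups, the serum progesterone level is not predictive of the outcome".

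For proportions, the Statistical analysis section names the chi-square test and Fisher's test ("exact test will be used for categorical variables"), two-sided, with P < 0.05 as significant. Separately, the Sample size calculation section says that age, BMI, endometrial thickness, serum E2 and number of transferred embryos were included in the analysis whatever their P values. It does not say which analysis is meant.

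**The concern.** The second reading settles in advance how one of the stated aims will be answered, and its logic has three weaknesses.

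- **No margin.** Comparable is undefined and the only tools named test for a difference. The natural working meaning is therefore not significantly different, which does not show absence of association.
- **A treated group in a prognostic question.** Group A1 has received extra progesterone. Its outcome reflects the low level and the treatment together. Only A2 v B isolates the relation of the measured level to outcome.
- **A non-randomised comparison.** A2 and B differ by serum level, not by allocation. Age, BMI or embryo stage could create a difference or hide one, and the article does not clearly assign covariate adjustment to this comparison.

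At stake is a published statement that serum progesterone is not predictive, made on data that could not exclude a sizeable association.

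**Working it through.** **Inputs.** From Sample size calculation: 134 in each of A1, A2 and B; clinical pregnancy rates 34.67% (low) and 51.55% (high), a gap of 16.88 points. On power, "The sample size was calculated in a two-sided test (80% statistical power, 95% confidence interval"; on alpha, "The significance level of the test was targeted at 0.05". From the Discussion: a cited cohort with ongoing pregnancy rates of 38% v 51%, at a different progesterone cut-off and with a vaginal gel. Assumed here: a 10-point difference (38% v 48%), and A1 midway between A2 and B.

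**Step 1. The plan's own figure.** With p̄ = (p1 + p2)/2,

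n = [1.96·√(2p̄(1−p̄)) + 0.8416·√(p1(1−p1) + p2(1−p2))]² / (p2−p1)².

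For 0.3467 and 0.5155 this is (1.96 × 0.7004 + 0.8416 × 0.6901)² / 0.1688² = 133.9, so 134. The stated size is reproduced, but the rates behind it are clinical pregnancy, whereas the sentence at issue concerns ongoing pregnancy.

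**Step 2. Precision of A2 v B.** The 95% half-width is 1.96·√[p(1−p)/134 + q(1−q)/134].

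- Both rates 28%: 10.8 points.
- Both rates 50%: 12.0 points.
- 38% v 51%: 11.8 points.

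**Step 3. How often A2 v B is non-significant when a difference exists.** Approximate power is Φ{[d√134 − 1.96·√(2p̄(1−p̄))] / √(p1(1−p1) + p2(1−p2))}, where d is the difference. For 38% v 51%: (1.505 − 1.96 × 0.7028)/0.6968 = 0.183, so power is 57% and the miss rate 43%. Simulation with binomial outcomes, 134 per group and uncorrected chi-square tests at 5% gives 42%. The table uses simulation throughout; the last column is a single 2-df chi-square across all three groups.

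| Rates A2 / A1 / B | Source | A2 v B non-significant | Three-group test non-significant |
|---|---|---|---|
| 34.67 / 43.11 / 51.55% | planning rates, A1 assumed | 19% | 29% |
| 38 / 44.5 / 51% | cited cohort, A1 assumed | 42% | 53% |
| 38 / 43 / 48% | assumed | 61% | 70% |

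**Step 4. What A1 does.** With A2 = 34.67% and B = 44.67%, the non-central chi-square power of the three-group test is 40% if A1 equals A2, 39% if A1 equals B, and 30% if A1 is 40%. A2 v B alone has 39%. A1 contributes nothing to the prognostic question, and it dilutes the three-group test when treatment has a partial effect.

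**Step 5. What a not-predictive claim would need.** For two one-sided tests at 5% with 80% power and no true difference, n per group = 2p(1−p)(1.645 + 1.282)²/margin². At rates of 35% to 45% this gives 174 to 189 for a 15-point margin, 390 to 424 for 10 points and 1,559 to 1,696 for 5 points. These margins are assumptions; the article gives none.

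**The case against.** The strongest reply is that the sentence is a conditional remark in a section on implications, not a decision rule in the analysis section. The trial's main question, A1 v A2 on ongoing pregnancy, is stated first and correctly. A reader might infer that the primary analysis is compromised. It is not: randomisation, the sample size and the A1 v A2 comparison do not depend on this sentence.

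A reader might also infer that including A1 makes false not-predictive conclusions more likely. That holds only if comparability means one three-group chi-square with A1 in between, and the article never names that test. If comparability means that all three pairs are non-significant, A1 makes the condition stricter: with 38 / 43 / 48%, all three pairs are non-significant 53% of the time, against 61% for A2 v B alone. Comparability of three groups also already entails comparability of A2 and B, so A1 is superfluous and sometimes diluting; it does not reverse the inference.

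Nor is it established that A2 v B would be unadjusted. The covariate sentence in Sample size calculation could refer to the trial or to the earlier retrospective data, and a detailed model may sit in a fuller document. What stands is that the two sections need reconciling.

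Finally, the error rate depends on the scenario. The 61% and 70% figures rest on a 10-point gap, smaller than any low-v-high difference the article reports (16.88, 13 and 20.3 points). At the planning rates A2 v B has about 80% power.

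None of this rescues the inference itself. With no margin, a non-significant result does not support a claim that the level is not predictive.

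**Conclusion.** The sentence is wrong as written, and it should be fixed as a secondary inference bearing on a stated aim. At 134 per group a non-significant A2 v B result leaves differences of roughly 11 to 12 points unexcluded even when the observed difference is zero. It would occur about 19% of the time at the planning rates, 42% at the cited 38% v 51% and 61% for a 10-point difference. These figures assume complete data at 134 per group and unadjusted chi-square tests. The first applies clinical pregnancy rates to an ongoing pregnancy question, the second borrows rates from a cohort with another cut-off, and the third is an assumption. Reading comparable as non-significant is itself an inference, though the only one that the stated methods allow.

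**What to change.** Replace the sentence in Expected repercussions with text to this effect:

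- The relation of day-3 serum progesterone to ongoing pregnancy will be assessed in the untreated groups only (A2 v B). It will be reported as a risk difference with 95% CI, adjusted for age, BMI, endometrial thickness, serum E2, number of transferred embryos and D3/D5 transfer stratum.
- A non-significant difference will be reported as inconclusive unless the interval excludes a difference fixed as relevant before outcomes are compared by group.
- The effect of added progesterone will be judged on A1 v A2 only.

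Also state in Statistical analysis whether the covariates listed under Sample size calculation belong to this comparison, so that the two sections agree.

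The cost is some wording and one regression on variables the article already names. The real price is in the claim. With a half-width of 11 to 12 points, a 95% interval cannot fit inside a margin of about 10 points or less, so at this sample size a finding of not predictive is effectively out of reach for such margins.
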